## Abstract

**Introduction**: Extended periods of sitting may have detrimental effects on brain health. However, the effects of breaking up prolonged sedentary periods with frequent, short physical activity bouts on mechanisms to improve brain health remain unclear. Therefore, this study aims to investigate the immediate effects of uninterrupted sitting and frequent, short bouts of physical activity on cerebral blood flow and cognitive function in the prefrontal cortex in middle-aged adults.

**Methods**: This is a protocol article to describe a randomized crossover study. We will collect data from 13 healthy adults, aged between 40 and 60 years old, with a body mass index <35 kg/m^2^. Participants will be required to come into the laboratory on three occasions, sit for 3 h, and perform a different type of break for 3 min every 30 min at each visit in a random order, being either: (1) a social break; (2) brisk walk on a treadmill; or (3) simple resistance activities. Before and after each experimental condition, cerebral blood flow (primary outcome) will be measured using functional near-infrared spectroscopy (fNIRS), with short-separation channels, and working memory (1-, 2-, and 3-back on the computer) will be assessed. The following additional secondary outcomes will be collected: psychological factors (questionnaires); arterial stiffness; salivary cortisol levels; and blood glucose levels.

**Conclusion**: The results from this randomized crossover study will determine the effects of uninterrupted sitting and frequent, short bouts of physical activity on cerebral blood flow and cognitive performance. Publication of this study protocol emphasizes the importance of registration and publication of protocols in the field of sedentary behavior research.

## Introduction

Sedentary behavior is gaining more attention owing to its association with increased risk of cardiovascular diseases and early mortality (Biswas et al., 2015; Patterson et al., 2018; Ekelund et al., 2019), and potential adverse effects on cognitive and mental health (Voss et al., 2014; Wheeler et al., 2017). Understanding the neurophysiological consequences of sedentary behavior is important considering that adults spend about two-thirds of their waking time and the majority of working hours in long periods of uninterrupted sitting (Parry and Straker, 2013).

Physical activity is known to promote healthy brain functions (i.e., cognitive and mental health; Angevaren et al., 2008; Hillman et al., 2008; Gomez-Pinilla and Hillman, 2013); and a candidate mechanism by which this can occur is through increased cerebral blood flow (Ogoh and Ainslie, 2009), particularly in the prefrontal cortex (Herold et al., 2018).

In light of the negative effects of sedentary behavior on vascular outcomes, it is possible that prolonged sitting may have adverse effects on brain health by reducing cerebral blood flow. However, sedentary behavior’s effects on cerebral blood flow, the mitigating effects of physical activity breaks, and what types of physical activity breaks remain unknown. A few studies, in younger- or older-aged populations, have demonstrated immediate improvements in cerebral blood flow from a single exercise session (Chang et al., 2012; Herold et al., 2018; Ji et al., 2019), whereas the influence of breaking up a sitting day with frequent (e.g., 30 min), short (e.g., 3 min) bouts of physical activity on increasing cerebral blood flow is less clear. Using a surrogate measure of cerebral blood flow (middle cerebral artery blood flow velocity), one study of healthy desk workers found immediate increases in blood flow velocity after short, frequent bouts of walking compared with uninterrupted sitting for 4 h (Carter et al., 2018). Also, in a study of older adults, middle cerebral artery blood flow velocity increased over a day of interrupted sitting with light-intensity walking breaks for 3 min every 30 min, after performing a 30-min moderate-intensity walk in the morning before the prolonged sitting time (Wheeler et al., 2019). However, another study of young adults found a reduction in cerebral blood flow and cognition after short, frequent bouts of calf raises over 3 h, compared to uninterrupted sitting for 3 h (Stoner et al., 2019). Finally, a study of 19 overweight and obese adults demonstrated improved fatigue after short, frequent bouts of light-intensity walking, which may be explained by improved cerebrovascular regulation, although this was not directly measured (Wennberg et al., 2016). Thus, results from previous studies are inconsistent and emphasize the need for further studies. Middle-aged adults may be at particular risk as low cerebral blood flow may contribute to future cognitive decline (Bertsch et al., 2009).

Moderate-to-vigorous intensity physical activity levels are often not attainable by most people and knowing the negative health effects of sedentary behavior, strategies to increase physical activity are needed that are manageable for long term (Dunstan et al., 2018). Earlier studies have demonstrated positive effects of frequent (e.g., 30 min), short (e.g., 3 min) breaks of physical activity on glycemic control (Dunstan et al., 2012; Dempsey et al., 2017), arterial health (Carter et al., 2019), middle cerebral artery velocity (Wheeler et al., 2019), fatigue (Wennberg et al., 2016), and cognitive performance (Wheeler et al., 2020). However, these feasible breaks have yet to be studied concerning simultaneously measured cerebral blood flow and cognitive performance.

Functional-near infrared spectroscopy (fNIRS) is an emerging neuroimaging technique that allows for accurate measurement of cerebral blood flow, such as in the prefrontal cortex (Herold et al., 2018). Other neuroimaging methods to measure cerebral blood flow, such as positron emission tomography and functional magnetic resonance imaging (fMRI) are cumbersome, due to the size and expense of the equipment, the need for participants to be supine, and high sensitivity to movement artifacts. By contrast, fNIRS is a more ecologically valid method to study cerebral blood flow, as measurement can be performed in various postures and settings. It is portable, non-invasive, cost-effective, and accurate when compared with fMRI measures (Huppert et al., 2006). One concern with fNIRS is that changes in superficial (i.e., extra-cerebral) blood flow may confound measures. Including short-separation channels in fNIRS systems allows the direct measurement of extra-cerebral blood flow thereby eliminating this as a confounder (Yücel et al., 2015), yet has rarely been used to date, but will be used in this study. In middle- and older-aged adults, vascular health and in particular arterial stiffness may moderate the effect of physical activity on cerebral blood flow (Elias et al., 2009; Tarumi et al., 2013) and is therefore also important to investigate.

The overall aim of this study is to explore the effect of uninterrupted sitting and frequent, short bouts of physical activity during a prolonged period of sitting on cerebral blood flow and cognitive function.

Our *primary* research question is:

1In middle-aged adults, what are the acute (immediate) effects of uninterrupted sitting and frequent, short activity breaks during 3 h of sitting on cerebral blood flow in the prefrontal cortex?Our *secondary* research questions are:2In middle-aged adults, what are the acute (immediate) effects of uninterrupted sitting and frequent short activity breaks during 3 h of sitting on:(a)Cognitive performance?(b)Psychological factors (stress, mood, alertness, and sleepiness)?(c)Post-prandial blood glucose?3Does vascular health (arterial stiffness) attenuate the effects of activity breaks on cerebral blood flow?Based on previous research, we hypothesize that:(a)Changes in neural activity-related prefrontal cortex cerebral blood flow (hereafter termed cerebral blood flow) from pre-test to post-test will be greater following the conditions with frequent, short activity breaks compared with the uninterrupted sitting condition;(b)Cerebral blood flow will be greater post-intervention compared to pre-intervention for the frequent, short activity breaks conditions, but not for the uninterrupted sitting condition;(c)Improvements in cognitive performance will be larger in magnitude in the frequent, short activity breaks conditions compared with the uninterrupted sitting condition;(d)The frequent, short activity break conditions will lead to improvements in psychological factors, compared with the uninterrupted sitting condition;(e)Glucose levels will not differ between the conditions;(f)Arterial stiffness will temporarily decrease immediately after the frequent, short activity break conditions (compared to pre-test levels), but will not change after the uninterrupted sitting condition; and(g)Arterial stiffness will moderate the effect of frequent, short activity breaks on cerebral blood flow, such that participants with lower arterial stiffness at baseline will have greater cerebral blood flow after the frequent, short activity break conditions compared with participants with higher arterial stiffness.

## Materials and Methods

### Design

A crossover randomized 3-condition experimental trial will be carried out with a target sample size of 13 participants. All study procedures will occur at the Swedish School of Sport and Health Sciences (GIH) in Stockholm, Sweden. Participants will be recruited from the general Swedish population using social media, GIH’s homepage, and newspaper advertisements. As well, through the Swedish Armed Forces’ personnel magazine and word of mouth. Participants will initially attend a familiarization session for the collection of demographic data, fitness testing, and acquaintance with experimental procedures. Each participant will undergo 3-h experimental conditions in random order, with a minimum washout period of 4 days between each of the three visits (Bell et al., 2018). Physical activity, sleep, and glucose levels will be measured for the 24 h before each condition. A computer-generated randomization schedule will be created before study commencement, and participants will be randomized to a condition order at the end of the familiarization session. This trial obtained ethical approval by the Swedish Ethical Review Authority, Stockholm, Sweden (Dnr 2019-00998). Trial registration for experimental studies of this nature is not required but is increasingly being recognized as good practice (English et al., 2020). Therefore, we registered this trial at www.clinicaltrials.gov (NCT04137211) on October 23, 2019, after recruitment began on May 13, 2019.

### Participants

We will include adults 40–60 years old, with a body mass index <35 kg/m^2^. People who have been diagnosed with diabetes, epilepsy, heart failure, stroke, or myocardial infarction, or other circulatory conditions will be excluded. Also, persons receiving current treatment for high blood pressure, sleep disorders, depression, or psychosis.

### Familiarization

Before randomization, participants will come to the laboratory at GIH for a familiarization visit where they will be introduced to all procedures of the study, including a practice of the cognitive tests. Demographic and other data to describe the sample will be collected including age, sex, height, weight, head circumference (to determine the optimal fNIRS cap-size), and a health screening questionnaire. Participants will also undergo an incremental treadmill test to establish their maximal oxygen uptake (VO_2max_) using a standard protocol and the OxyCon Pro metabolic system (Erich Jaeger GmbH, Hochenberg, Germany). The results of the fitness test will be used to determine the intensity of the walking break condition.

### Pre-experimental Day Monitoring

To standardize the 24 h before each test day, participants will be advised to abstain from any physical activity and alcohol intake and will be asked to record details about their physical activity and sleep in a standardized diary. Participants will also wear activity monitors during this period to collect objective data about physical activity (hip-worn actigraph GT3X+ and activPAL micro) and sleep (wrist-worn actigraph GT3X+). Physical activity variables from the actigraph will include total physical activity and percentages of wear time spent in sedentary, light, and moderate-to-vigorous physical activity, according to standardized cut-points (Sasaki et al., 2011; Aguilar-Farias et al., 2014). Physical activity variables from the activPAL micro monitor will include time spent sitting including in prolonged bouts (>20 min), number of breaks from sitting each hour and time spent standing, stepping, and intense stepping. During night time, participants will wear the actigraph GT3X+ on the non-dominant wrist (Cellini et al., 2013). Using the existing Cole-Kripke algorithm (Cole et al., 1992), the following key aspects of sleep will be calculated: time to sleep onset, sleep efficiency, times waking up after sleep onset, and total sleep.

To standardize dietary intake and blood glucose levels, participants will be asked to record their dietary intake for the 24 h before each condition in a standardized food diary and closely match their diet for each pre-condition day. They will also be asked to fast and abstain from caffeine after dinner the night before. Additionally, participants will wear a continuous blood glucose monitor (Abbott FreeStyle Libre sensor) during the 24 h before, and during each experimental condition.

### Experimental Conditions

To minimize physical activity the morning of the visit participants will be transported to the laboratory *via* taxi. On the morning of testing, participants will be asked to provide four saliva samples (for cortisol testing); immediately after waking and at 30, 45, and 60 min thereafter. Once they arrive at the laboratory, pre-condition outcome measures will be collected, followed by an individually standardized breakfast (consisting of maximum two slices of bread with butter and cheese, a bowl of yogurt, a banana, and a glass of water), with no specific time restriction for eating. Participants at their initial visit will be advised to eat their preferred amount, which will be subsequently weighed and recorded. The portion sizes will be then replicated at each visit. The activPAL activity monitor and glucose monitor will be worn during the experimental conditions to monitor sitting time during the test day.

The three experimental conditions (summarized in Figure 1) are: (A) uninterrupted sitting for 3 h with a 3-min social break every 30 min (SOCIAL); (B) sitting for 3 h with a 3-min bout of moderate-intensity walking on a treadmill every 30 min (WALK), or (C) sitting for 3 h with a 3-min bout of simple resistance activities every 30 min (SRA). During the sitting, participants will be permitted to read a book and drink water, but not use any technological devices or doze off. The SOCIAL break (condition A) will consist of a 3-min chat between the research staff and the participant. The WALK break (condition B) will be performed at moderate intensity (75–80% of maximal heart rate), normalized to individual participants’ VO_2max_ (see Supplementary Material). For the SRA break (condition C), participants will be asked to complete 20-s bodyweight half-squats, 20-s calf raises, and 20-s gluteal contractions and knee raises repeated three times in sequential order by following standardized video instructions (as per Dempsey et al., 2017). At 135 min after the experimental condition commences, participants will be offered a toilet break.

**Figure 1 F1:**
[figure not shown]
Experimental day procedures of the three conditions after a standardized breakfast. Condition A: 3 h of sitting with 3-min social breaks every 30 min (SOCIAL); Condition B: sitting 3 h with a 3-min bout of brisk walking on a treadmill every 30 min (WALK); Condition C: sitting for 3 h with a 3-min bout of simple resistance activities every 30 min (SRA). WC: toilet break; fNIRS, functional near-infrared spectroscopy.

### Outcome Measures

Outcome measures will be collected immediately before and immediately after each experimental condition.

#### Cerebral Blood Flow

The primary outcome measure will be the changes in oxygenated hemoglobin (oxy-Hb) using a non-invasive multi-channel continuous-wave fNIRS instrument (portable NIRSport, 8–8 system, with short-separation channels, NIRx Medizintechnik GmbH, Berlin, Germany). The optodes will be positioned over the prefrontal cortex, with data sampled at 7.81 Hz at wavelengths 750 nm and 820 nm. The fNIRS cap has 16 channels created by eight LED light sources and 8 detectors placed according to the standard 10–20 system, with a source-detector separation distance of 3 cm. Additional short-separation optodes with a distance of 0.8 cm (NIRx Medizintechnik GmbH, Berlin, Germany) to account for superficial blood flow (Yücel et al., 2015) will also be used. We chose to measure cerebral blood flow in the prefrontal cortex region as working memory tasks (such as the n-back) predominately activate this region (Smith and Jonides, 1997; Owen et al., 2005). System calibration will be performed before each assessment using NIRStar 15.2 software and using the predefined montage, and the fNIRS signals will be visually quality checked during data collection for motion artifacts. Cerebral blood flow measures will be taken simultaneously while the participant performs three cognitive tasks of increasing workload (numerical 1-, 2-, and 3-back tests). Our primary outcome variables will be changes in oxy-Hb between the 1-back and 2-back and between the 1-back and 3-back tests (expressed in ΔμM). We will also record deoxygenated (deoxy-Hb) concentrations. Further details about system calibration and data processing are included in Supplementary Material.

#### Cognitive Performance

Cognitive performance in working memory will be assessed using a computerized n-back test (Kirchner, 1958), consisting of the 1-, 2-, and 3-back tests administered simultaneously with fNIRS measures. We will use a computerized, numerical version of the n-back, whereby participants will be required to indicate (*via* a keypress within 2 s from stimulus onset) whether the digit presented on the screen was the same as the digit presented 1 stimulus previously (1-back), 2 stimuli previously (2-back), or 3 stimuli previously (3-back). Each digit will be presented for 1.5 s at an interstimulus interval of 500 ms. The n-back tests were created using E-Prime 2.0 (Psychology Software Tools). To reduce practice effects, participants will perform practice tests before data collection on each experimental day. The outcome variables for cognitive performance will include average reaction time (ms) and accuracy (average number of correct responses) for each test across two blocks of 20 digit sequences (1-back) or four blocks of 20 digit sequences (2- and 3-back).

#### Arterial Stiffness

Arterial stiffness will be measured using SphygmoCor Technology (Butlin and Qasem, 2017). The technology is a non-invasive, reproducible, and accurate method that uses waveform shape parameters from the radial artery to acquire central aortic blood pressure waveform. The aortic pressure waveform will be derived from the radial waveform by a validated transfer function (Pauca et al., 2001). Briefly, after 5 min of supine rest (only at pre-test), high fidelity pressure waveforms will be recorded (three times). The measurements will be ended when all quality parameters (pulse height variation, pulse length variation, diastolic variation, and shape deviation) are fulfilled in the SphygmoCor equipment (SphygmoCor, AtcorMedical, Sydney, Australia; Nelson et al., 2010). The variable for arterial stiffness will be the average of the augmentation index (AIx) across the three measures.

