### Sample Size

Several studies (Hyodo et al., 2012; Endo et al., 2013; Byun et al., 2014; Bediz et al., 2016; Carter et al., 2018; Kujach et al., 2018; Ichinose et al., 2020) on the acute effects of light, moderate, and intense physical activity on post-exercise cerebral blood flow have been performed on similar, but not identical, designs and interventions as in our study, but have used comparable populations. Data from these studies were used to recalculate effect sizes using G*Power software (Franz Faul, Universität Kiel, Germany, v 3.1.9.2). Results showed effect sizes between 0.9 and 2.4, rendering a minimum sample size of between 6 and 13 individuals with an *α* = 0.05 and *β* = 0.8 assuming a two-tailed test. We chose to match our sample size to the largest found among the reviewed studies, namely 13 subjects.

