### Data Analysis

To answer our primary research question, linear mixed-effects models with subject as the random effect will be used to assess within condition differences in the changes in cerebral blood flow (oxy-Hb) between pre- and post-tests correcting for multiple comparisons from estimation over many channels, using Benjamini–Hochberg. Time and condition interactions will be used to estimate differences between conditions. Baseline arterial stiffness will be assessed as a moderator in the models. Linear mixed models will also be used to assess secondary outcomes, to investigate within-person changes from pre- to post-test, and between conditions. Stata version 15 (StataCorp, College Station, TX, USA) and NIRSToolboxAnalyzer (Santosa et al., 2018) will be used for statistical analyses.

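### Arterial stiffness is recorded after supine rest at pre-test only, so the within-condition pre-to-post change in hypothesis (f) is mixed with a change in measurement state

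*Protocol article*

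**What the plan says.** The Arterial Stiffness section specifies that "after 5 min of supine rest (only at pre-test), high fidelity pressure waveforms will be recorded". The outcome is defined there as follows: "The variable for arterial stiffness will be the average of the augmentation index (AIx) across the three measures". The opening of Outcome Measures sets the timing: "Outcome measures will be collected immediately before and immediately after each experimental condition".

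Hypothesis (f), at the end of the Introduction, is worded as a within-condition comparison: "Arterial stiffness will temporarily decrease immediately after the frequent, short activity break conditions (compared to pre-test levels), but will not change" after uninterrupted sitting. For secondary outcomes, Data Analysis plans linear mixed models "to investigate within-person changes from pre- to post-test, and between conditions".

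Two other sections fix the nutritional state. Pre-experimental Day Monitoring asks participants to fast after dinner the evening before. Experimental Conditions places the pre-condition measures on arrival and breakfast after them. The pre-test is therefore fasted and the post-test fed. Breakfast portions are recorded at the initial visit and repeated at each visit.

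**The concern.** A pre-to-post change is attributable to the condition only if the two readings are taken in the same way. Here the article states that they are not. The rest step is present at one time point and absent at the other, and feeding differs in the same direction of time. In each condition, time and measurement state change together, so no model of the pre and post values from that condition can separate them.

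Hypothesis (f) depends on exactly this comparison, in two ways. It predicts a fall after each activity condition, and it predicts no change after sitting. An offset in one direction adds to or imitates the fall. An offset in the other direction hides it. Either direction disturbs the prediction for sitting. The bias is a constant, so a larger sample does not reduce it; it only makes it more likely to reach significance.

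**Working it through.** **Inputs.** From Sample Size: n = 13, two-sided α = 0.05, target power 0.8 (printed there as β), and effect sizes given as "Results showed effect sizes between 0.9 and 2.4", "rendering a minimum sample size of between 6 and 13 individuals". These effect sizes concern post-exercise cerebral blood flow. The article gives no effect size for arterial stiffness and no figure for the effect of omitting rest. The offset below is therefore an assumption, varied over a range and expressed in SDs of the pre-to-post change.

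**Method.** A paired t-test stands in for the within-condition contrast of the mixed model. With δ the mean change divided by the SD of the change,

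P(significant) = P(|T| > t(0.975; n − 1)), where T is noncentral t with n − 1 degrees of freedom and noncentrality δ√n.

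For n = 13, t(0.975; 12) = 2.179 and √13 = 3.606.

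**The plan's own figure.** At δ = 0.9 the smallest n with 80% power is 12 (power 0.810), and n = 13 gives 0.845. At δ = 2.4 the smallest n is 4, against the stated 6. The stated range is reproduced to within two participants, so the method is close to the one used. The point does not depend on this figure.

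**No true change, offset only.**

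| Offset (SD of change) | Noncentrality | Chance of a significant within-condition change |
|---|---|---|
| 0 | 0 | 5% |
| 0.25 | 0.90 | 13% |
| 0.5 | 1.80 | 38% |
| 0.75 | 2.70 | 70% |
| 1.0 | 3.61 | 91% |

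**True decrease of 0.9 SD, offset working against it.** The net shift is 0.9 minus the offset.

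| Opposing offset | Net shift | Chance of detecting the decrease |
|---|---|---|
| 0 | 0.90 | 85% |
| 0.25 | 0.65 | 58% |
| 0.5 | 0.40 | 26% |
| 0.75 | 0.15 | 7% |

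**Can an offset alone produce the full pattern in (f)?** Let p be the chance that a common offset gives a significant decrease in one condition. With no true effect, and assuming independence across visits, the pattern (decrease, decrease, no significant change) has probability of at most p²(1 − p). This is largest at p = 2/3: (4/9)(1/3) = 4/27 = 15%. At p = 0.8 it is 0.8 × 0.8 × 0.2 = 13%.

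**Between-condition contrast.** Write the observed change as true change + offset. Then

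(change in WALK + offset) − (change in SOCIAL + offset) = change in WALK − change in SOCIAL.

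The offset cancels if it is the same in both conditions. The same holds for simple resistance activities against SOCIAL.

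**The case against.** The strongest case on the other side has four parts.

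*The crossover already deals with it.* Data Analysis includes comparisons between conditions, in which a common offset cancels, and the repeated breakfast makes feeding common to all visits. This is right, and it is why the remedy is small. But (f) is worded within condition, and the same section also analyses within-person change, so the affected comparison remains part of the plan.

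*The asymmetry may be deliberate.* Participants have just arrived at pre-test but have sat for most of 3 h by post-test, and a rest period could dilute an effect that (f) calls temporary. This is plausible, but the article gives no such reason, and the two readings would still not be taken in like states.

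*The offset cannot confirm (f).* A reader might infer that the measurement procedure alone could confirm the hypothesis. The calculation does not support that: a common offset moves all three conditions together, so the full pattern arises with probability of at most about 15%. The offset can readily mask an effect or disturb individual parts of (f).

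*Heart rate is conjecture.* A reader might also infer that the between-condition contrast is biased because heart rate stays raised after activity. The article does not mention heart rate in connection with the augmentation index. Its text does not give the interval from the last break to the recording; the schedule is in a figure not available here. The n-back tests alone take about 6.7 min (10 blocks × 20 digits × 2 s), and their order relative to the stiffness recording is not in the text. An unequal offset is possible but not shown.

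**Conclusion.** The point holds for the within-condition reading of hypothesis (f). The difference in rest is stated outright, the fasted and fed states follow from the schedule, and nothing in the article corrects or explains them. The false-positive figures of 13%, 38% and 70% rest on assumed offsets of 0.25, 0.5 and 0.75 SD and on a paired t-test as a stand-in for the mixed model. They show how sensitive the comparison is, not how large the bias will be.

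The scope is narrow. Arterial stiffness is not the primary outcome, so the oxy-Hb analysis and the sample size are untouched. Hypothesis (g) uses baseline stiffness, which is measured after rest, and is unaffected. This is a change that should be made, but it does not threaten the trial's main conclusion.

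**What to change.** 1. Name the time-by-condition contrast as the test of (f): the change in WALK minus the change in SOCIAL, and the change in the resistance condition minus the change in SOCIAL.
2. Drop the conclusions that stiffness fell within a condition or stayed unchanged after sitting, or label those results descriptive.
3. State the rest asymmetry and the fasted and fed states as a limitation, and add that the contrast is protected only if the offset is similar across conditions.
4. Use heart-rate adjustment at most as a sensitivity analysis, and only if the rate is available from the recording. Heart rate at post-test may itself be affected by the condition, so adjusting for it changes the quantity estimated.
5. Do not change the rest procedure part-way through. Recruitment had already begun, and two measurement procedures among 13 people would add a further difference.

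The cost is analysis wording and some precision. If the changes have equal SD and correlation r between visits, an effect of 0.9 SD of the change becomes 0.9/√(2(1 − r)) SD of the difference in changes. That is 0.64 at r = 0 (power 56% with n = 13) and 0.90 at r = 0.5 (85%); r is assumed, as the article does not give it. No extra visits or measurements are needed.

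### Arterial stiffness is defined as the augmentation index with no heart-rate standardisation, so any heart rate still raised at post-test would bias hypothesis (f) towards the predicted fall

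*Protocol article*

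**What the plan says.** All places are in the protocol article.

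- **Arterial Stiffness** defines the variable: "The variable for arterial stiffness will be the average of the augmentation index (AIx) across the three measures". The recording procedure is: "after 5 min of supine rest (only at pre-test), high fidelity pressure waveforms will be recorded (three times". Supine rest is thus specified before the first measurement and not before the second.
- **Introduction, hypothesis (f)**: "Arterial stiffness will temporarily decrease immediately after the frequent, short activity break conditions". The comparison is with pre-test. For the sitting condition the hypothesis adds: "but will not change after the uninterrupted sitting condition".
- **Introduction, hypothesis (g)**, and **Data Analysis**: baseline arterial stiffness is also a moderator in the cerebral blood flow models.
- **Experimental Conditions**: the walking break is "performed at moderate intensity (75–80% of maximal heart rate" (the parenthesis is cut short here). The resistance break consists of bodyweight exercises, with no heart-rate figure given. The social break is a conversation.
- **Outcome Measures**: "Outcome measures will be collected immediately before and immediately after each experimental condition".
- **Data Analysis**: secondary outcomes go into linear mixed models, from pre to post and between conditions. No heart-rate term is named.

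**The concern.** AIx describes how far the reflected pressure wave adds to the systolic peak. A faster heart shortens ejection, so the reflected wave arrives relatively later in systole and AIx falls although the vessel wall is unchanged. This is general knowledge about the index. The documents do not state it.

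The design lets heart rate vary along the contrast that is tested. Two conditions include repeated exercise and one does not, and the second reading has no required rest. If heart rate is still above its pre-test level when the post-test waveform is recorded, AIx will be lower for that reason alone. Residual exercise heart rate would give the pattern that hypothesis (f) predicts: a fall after the activity conditions and little change after sitting. Comparison with the social condition would not remove it, because the residual elevation is what differs between conditions. The hypothesis could then be declared supported with no change in stiffness.

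**Working it through.** **The plan's own figure.** The plan gives no figure for AIx. Its only calculated figure is the sample size of 13, derived for cerebral blood flow. A two-sided paired t-test at 5% with d = 0.9 and 80% power needs 12 participants (power 0.845 at 13), close to the stated 13. That figure is not disputed and serves here only as N.

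**Inputs**

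- N = 13, two-sided α = 0.05 (Sample Size).
- True change in stiffness = 0 (set, to isolate the artefact).
- Slope b of AIx on heart rate: 0.3 to 0.5 points lower per extra beat/min (assumption).
- Post-minus-pre heart-rate difference ΔHR: 0 to 15 beats/min (assumption; zero is included because recovery may be complete).
- SD of the pre-post change in AIx: 4 to 8 points (assumption).

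**Step 1: spurious change.** Spurious change = −b × ΔHR.

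- ΔHR = 0: 0 points.
- ΔHR = 5, b = 0.3: 0.3 × 5 = 1.5 points lower.
- ΔHR = 15, b = 0.5: 0.5 × 15 = 7.5 points lower.

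**Step 2: chance of a false significant change.** A paired t-test within one condition stands in for the mixed-model contrast. The noncentrality is √13 × (b × ΔHR) / SD, with 12 degrees of freedom and critical value 2.179. Two worked cases:

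- b = 0.3, ΔHR = 5, SD = 8: √13 × 1.5 / 8 = 0.68, rejection about 10%.
- b = 0.5, ΔHR = 10, SD = 4: √13 × 5 / 4 = 4.51, rejection about 98%.

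| ΔHR (beats/min) | Spurious fall (points) | Chance of p < 0.05 |
|---|---|---|
| 0 | 0 | 5% |
| 2 | 0.6 to 1.0 | 6 to 13% |
| 5 | 1.5 to 2.5 | 10 to 54% |
| 10 | 3.0 to 5.0 | 24 to 98% |
| 15 | 4.5 to 7.5 | 46 to 100% |

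Everything depends on ΔHR at the time of recording. At 0 to 2 beats/min the artefact is negligible or small. From about 5 beats/min it can matter, and at 10 or more it can dominate.

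**Step 3: what standardisation leaves.** If the correction uses slope c while the true slope is b, the remaining error is (b − c) × ΔHR. With c = 0.4, the middle of the assumed range, the worst case is 0.1 × 15 = 1.5 points in either direction, against 7.5 points uncorrected.

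**The case against.** **The article is a condensed account.** It never says that AIx is unadjusted, and the choice of AIx output or model covariates might sit in a fuller document. A reader might infer that the investigators have ruled out standardisation; the text does not show that. Still, the article does define the variable, and that definition, followed as written, carries the problem. So this is more than an omitted detail.

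**Heart rate may have recovered.** The measurements follow the 3-h condition, not necessarily an exercise bout. Breaks last 3 min and recur every 30 min, so the last bout could end well before post-test. The n-back session alone takes 10 blocks × 20 digits × 2 s = 400 s, about 6.7 min, and might come before the AIx recording. Neither the interval from the last break nor the order of the post-tests is in the text, and Figure 1 is not shown. This stands in full and is why the range must include zero. A reader might also take the walking intensity as the heart rate at recording. It describes the bout only. For the resistance condition there is no heart-rate figure at all.

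**The missing post-test rest applies to every condition.** This is true. It affects each pre-post contrast, the sitting condition included, and does not by itself separate the conditions. Residual exercise heart rate is what would separate them.

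**A heart-rate covariate is no clean remedy.** This also stands: post-test heart rate is affected by the condition, so adjusting for it changes what hypothesis (f) estimates.

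**The moderator argument is weak.** Baseline AIx is taken after supine rest and before any activity, so the exercise artefact does not reach it. What remains is that resting heart rate differs between people.

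**Conclusion.** The point holds as a risk of bias in a secondary outcome. As defined, AIx cannot separate a change in the artery from a change in heart rate, and any residual elevation biases hypothesis (f) towards the predicted decrease. The size is unknown: zero with full recovery, and 1.5 to 7.5 AIx points if the slope is 0.3 to 0.5 points per beat/min and the residual elevation is 5 to 15 beats/min. The false-positive chances also rest on the assumed SD of 4 to 8 points.

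Two stronger conclusions are tempting. One is that a fall in AIx in this trial must be an artefact; the documents give no heart rate at post-test, so this cannot be said. The other is that the primary result is compromised; the oxy-Hb contrast between conditions does not use AIx except through the moderator, and there the concern is minor.

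**What to change.** 1. In Arterial Stiffness, define the outcome for hypothesis (f) as AIx standardised to a fixed heart rate (for example 75 beats/min), computed for each recording and then averaged over the three.
2. Report unstandardised AIx and heart rate beside it at each time point and condition, so that readers can see whether heart rate had recovered.
3. Use heart rate as a model covariate only in a sensitivity analysis, for the reason given above.
4. For consistency, use the same standardised baseline AIx as the moderator for hypothesis (g).
5. Word conclusions as a change in augmentation index (wave reflection), not in stiffness itself.

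The cost is one changed definition and some extra reporting. Heart rate is contained in the recorded waveforms, so no measurement or participant is added and the sample size stays at 13. The small downside is reliance on a linear heart-rate correction, which showing the unstandardised value makes open to inspection. If heart rate has recovered by post-test, the change does little and does no harm.
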